## Abstract

**Background:**

The underlying mechanisms of non-specific chronic neck pain relapses are not clear, but they could be associated with a deficit and alteration of neck muscles propioception that play a decisive role in cervical joint position, motor control of the head, and postural stability. Numerous treatments for non-specific chronic neck pain have been described in the scientific literature. However, few studies analyze its influence on postural stability, since these alterations are not fully described, and various theories emerge about the reasons that cause it. Our primary aim is to analyze the differences in postural stability, pain, cervical disability, and the relation between them produced by a treatment based on manual therapy and another based on therapeutic exercise.

**Methods:**

The short-term and mid-term changes produced by different therapies on subjects with non-specific chronic neck pain will be studied. The sample will be randomly divided into three groups: manual therapy, therapeutic exercise, and placebo. As dependent variables of the study, we will take (1) Overall Balance Index, measured through a dynamic stabilometric platform; (2) pain, based on the visual analog scale and the Pressure Pain Threshold; (3) cervical disability, through the neck disability index. The findings will be analyzed statistically considering a 5% significance level (*p* ≤ 0.05).

**Discussion:**

Our study aims to provide knowledge about postural stability and its relationship with pain in subjects with non-specific chronic neck pain. Analyzing the results produced by different types of therapy will allow us to draw conclusions about the mechanisms, structural or central, that may elicit these alterations.

**Trial registration:**

Brazilian Clinical Trials Registry, RBR-2vj7sw. Registered on 28 November 2018.

**Electronic supplementary material:**

The online version of this article (10.1186/s13063-019-3598-7) contains supplementary material, which is available to authorized users.

## Background

Non-specific neck pain is pain that does not show pathognomonic signs and symptoms [1]. When the duration of symptoms is greater than 12 weeks of evolution, it acquires the value of chronicity and is denominated non-specific chronic neck pain (NCNP) [2]. It is a common disorder, which generates a great impact and socio-economic cost [3].

The underlying mechanisms of NCNP relapses are not clear, but the pain could be associated with a deficit and alteration of the proprioception of the neck muscles that play a decisive role in the cervical joint position, motor control of the head, muscles, and eyes, and postural stability (PS) [4–6].

Patients with NCNP usually have alterations in cervical proprioception and PS. They may also develop symptoms such as dizziness or vertigo [7, 8]. A recently published study shows that patients with NCNP suffer greater sensations of stunning and lack of proprioception than patients with benign paroxysmal vertigo [9].

Numerous studies downplay the efficacy of manual therapy and therapeutic exercise for pain reduction, cervical disability, and associated symptoms, such as dizziness [10–12]. However, there is less evidence of how these treatments, common in clinical practice, influence PS [13].

PS is highly influenced by the upper cervical spine and the suboccipital muscles, which are composed of up to 200 neuromuscular spindles per gram of muscle [14, 15]. This upper cervical segment is connected to the central nervous system (CNS), visual and vestibular apparatus, and sympathetic nervous system [16–19] in addition to cervical afferents through the cervico-ocular reflex (COR), the cervico-collic reflex (CCR), and the tonic neck reflex (TNR). The CCR activates the cervical musculature in response to stretching, maintaining good head position [20]; the COR acts through the vestibular reflex and the optokinetic reflex [21]. Finally, the TNR added to the vestibulospinal reflex achieves the maintenance of PS [22].

The alteration of this proprioceptive complex is not completely defined. Various theories have tried to explain how this system can be altered. Some studies indicate that there is a proprioceptive alteration due to sustained exposure to pain that affects PS through the CNS; these changes may be due to changes in the cortical representation and modulation of the cervical afferent contribution [23, 24]. In addition, some authors have begun to point out other psychobehavioral causes that could have a great influence on PS, such as anxiety, depression, or fear of movement [5, 6]. We must bear in mind that these variables are present in numerous patients with NCNP [25, 26].

However, other researchers relate the loss of PS to the dysfunction of the upper cervical spine and its musculature, changes in the cervical mechanoreceptors, and the state of weakness of the musculature [27–29], but these are not necessarily associated with traumatic events, since these types of alterations have been identified among subjects with NCNP without exposure to trauma [29].

The area of dizziness of cervicogenic cause is quite unknown; there are several theories about its cause, and there is no consensus on the diagnostic criteria [30]. More research is needed about relationships between neck pain, PS, and cervicogenic dizziness.

### Primary objective

The aim of our study is to compare two scientifically approved therapies for NCNP—one treatment with a greater influence on the structural component, and the other one with a greater component on the central process—to observe differences in the PS of the subjects with NCNP.

### Secondary objective

A secondary objective is to analyze the evolution of cervical pain and disability according to the treatment applied and the relationship with changes produced on PS.

### Hypothesis

Experimental treatments have a greater beneficial effect on PS and pain of subjects with NCNP than sham treatment. The improvement in PS is linked to an improvement in the subject’s pain.

### Trial design

This study is a randomized, controlled, parallel, double-blind, three-arm clinical trial of treatment.

## Methods/design

### Sample selection

Individuals with NCNP will be recruited through a text message broadcast on social networks in the city of Seville (Spain) and will be selected based on the eligibility criteria listed below. The study will take place in the facilities of the physiotherapy department of the University of Seville.

### Inclusion criteria

The inclusion criteria are:Age 18–50 yearsCurrent neck painNeck pain continued for at least the last 12 weeks [2].

### Exclusion criteria

The exclusion criteria are:Irradiated neck painNeck pain associated with vertigoOsteoporosisPsychological disordersVertebral fracturesTumorsMetabolic diseasesPrevious neck surgeryRed flags (Night pain, severe muscle spasm, loss of involuntary weight, symptom mismatch)Physiotherapeutic treatment continued in the last 3 months

### Interventions

The participants can only receive the assigned treatment; they cannot combine the treatment with drugs or other physiotherapeutic treatment. Any interference in the treatment will be grounds for exclusion.

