#### Group 3: sham treatment

For the “control” protocol, the patient will be placed in the supine position, while the physiotherapist will lay his hands without therapeutic intention on the patient’s neck for 3 min, the physiotherapist will simulate the technique of suboccipital inhibition [34]. Later, with the laser pointer off, the patient will be contacted without exerting pressure for 10 s. Patients assigned to the control group will receive treatment 1 or 2 after completing the study.

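### Use of drugs or other physiotherapy after allocation is grounds for exclusion, with no statement of exclusion from what or until when; read as removal from the study, it undermines the randomised comparison

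*Protocol article*

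**What the plan says.** The Interventions section of the protocol article limits participants to their assigned treatment: "they cannot combine the treatment with drugs or other physiotherapeutic treatment". The consequence follows directly: "Any interference in the treatment will be grounds for exclusion".

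This is not an entry criterion. Those are listed in their own sections, and prior treatment is covered there: "Physiotherapeutic treatment continued in the last 3 months". The Interventions rule concerns people who already have an assigned treatment in a randomised, parallel, three-arm trial.

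The Hypothesis section states what the trial expects: "Experimental treatments have a greater beneficial effect on PS and pain of subjects with NCNP than sham treatment", and "The improvement in PS is linked to an improvement in the subject’s pain". Treatment lasts three weeks in the manual therapy and exercise arms. Outcomes are measured before treatment and at weeks 2, 4 and 12. The Statistical analysis section compares the groups by one-factor ANOVA or Kruskal-Wallis. Nothing in the article says that a participant who is excluded is still followed or analysed.

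**The concern.** Randomisation makes the three groups comparable at the start. A rule that removes people because of something they do after allocation keeps that comparability only if the removal is unrelated to both arm and outcome. Here it plausibly relates to both. A participant whose neck pain persists has more reason to take an analgesic or seek other physiotherapy. If the trial's hypothesis is right, such participants will be more common in the sham arm, where "the physiotherapist will lay his hands without therapeutic intention on the patient’s neck for 3 min". Pain is itself an outcome, and the hypothesis links it to the balance outcome.

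If these participants leave the study, the sham group that is analysed has lost some of its worst cases, and the between-group test no longer compares the groups as randomised. The wording must also be settled early. An analysis plan can define an as-randomised set, but it cannot recover week 4 and week 12 measurements that were never taken.

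**Working it through.** **What the text fixes and leaves open**

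| Question | Protocol article |
|---|---|
| When does the rule apply? | After allocation (Interventions; entry criteria are separate) |
| What triggers it? | Drugs, other physiotherapy, any interference |
| Excluded from what? | Not stated |
| Until when? | Not stated: the 3 weeks of treatment or the 12 weeks of follow-up |
| Are excluded participants still measured and analysed? | Not stated |

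The plan gives no expected rate of exclusion, so it has no figure of its own to reproduce on this point. What follows is an illustration.

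**Inputs from Sample size calculation**
- Minimum difference in OBI 0.098 and SD 0.10, so the planned effect is 0.098 / 0.10 = 0.98 SD.
- 66 participants in three groups: 66 / 3 = 22 per group.
- Allowance for follow-up losses 15%: 0.15 × 22 = 3.3 per group.

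**Assumptions (none is in the documents)**
- Exclusion removes everyone whose pain exceeds a common threshold, set so that a fraction q of the sham arm is removed; q = 10%, 20% or 30%.
- Active treatment improves pain by 0.98 SD, borrowed from the OBI effect.
- Pain and OBI are normally distributed with correlation r = 0.3 to 0.8 within each arm.

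**Formulas.** With threshold c = z(1−q), dropping the upper tail lowers the mean pain of those who remain by:
- sham: A = φ(c) / Φ(c)
- active: B = φ(c + 0.98) / Φ(c + 0.98)

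The OBI mean of each arm moves by r times its pain shift, so the estimated OBI difference is 0.98 − r(A − B).

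**Worked case, q = 20%**
- c = 0.8416; A = 0.2800 / 0.80 = 0.350.
- Active threshold 0.8416 + 0.98 = 1.8216; fraction excluded 3.4%; B = 0.0759 / 0.9657 = 0.079.
- A − B = 0.271.
- r = 0.3: 0.98 − 0.081 = 0.90 SD. r = 0.8: 0.98 − 0.217 = 0.76 SD.
- Relative loss: 0.081 / 0.98 = 8% to 0.217 / 0.98 = 22%.

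| Sham excluded | Active excluded | A − B | Estimated OBI effect, r = 0.3 to 0.8 (true 0.98 SD) |
|---|---|---|---|
| 10% | 1.2% | 0.164 | 0.93 to 0.85 SD |
| 20% | 3.4% | 0.271 | 0.90 to 0.76 SD |
| 30% | 6.6% | 0.359 | 0.87 to 0.69 SD |

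Simulation of the same model agrees with these values to within 0.01 SD. If treatment changed pain but had no effect on OBI, the same r(A − B) would appear as a spurious OBI difference in favour of sham: 0.08 to 0.22 SD at q = 20%.

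**Numbers left.** At q = 20% the sham arm would lose 0.20 × 22 = 4.4 participants to this rule alone, against an allowance of 3.3 for follow-up losses. No separate allowance for exclusions is stated.

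**The case against.** The strongest reply is that the sentence fixes less than it seems to. Grounds for exclusion is not the same as a statement that participants are excluded, and the object of the exclusion is not named. It could mean stopping the assigned treatment only. This is also a journal article, analysis populations are commonly left to an analysis plan, and their absence here is no fault. That stands as a limit: the point rests on the sentence that is stated and on its natural reading, not on a missing intention-to-treat definition.

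Second, the rule speaks of combining and interfering with the treatment, which lasts three weeks. If it lapses then, there is less time to seek other relief, and exclusion rates of 20% or 30% become harder to defend. This also stands, and is one reason the time span needs stating.

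Third, the primary objective as worded compares the two active therapies, whereas the illustration concerns active against sham. There the illustrated bias works against the trial's hypothesis, so it would not produce a false claim of benefit. Both observations are correct, but an understated effect is still a wrong estimate.

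Two stronger readings are tempting and should be resisted:
- A reader might set the 0.35 SD shift in sham pain at q = 20% against the planned 0.98 SD and conclude that over a third of the effect is lost. That compares a pain shift in one arm with an OBI difference between arms. After allowing for the correlation and for exclusions in the active arm, the loss is 8% to 22%, still under assumed rates.
- A reader might cite the sham section, "Patients assigned to the control group will receive treatment 1 or 2 after completing the study", as evidence that sham participants will look elsewhere. It says nothing about exclusion or co-treatment during the trial, and the promise of later treatment could equally reduce such behaviour.

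**Conclusion.** The concern holds in this form: the protocol states a post-randomisation exclusion rule, leaves its object and duration undefined, and on the natural reading allows outcome-related removal from a randomised comparison. That the removal depends on arm and outcome is an inference, but one drawn from the trial's own hypothesis, its sham control and its pain outcome.

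Neither the size nor the direction of the bias can be derived from the documents. Under the assumptions above, 20% exclusion in the sham arm turns a true 0.98 SD OBI effect into about 0.90 to 0.76 SD. Lower exclusion rates or a weaker pain-OBI correlation would give less. No figure is offered for manual therapy against exercise. The sentence should be corrected before follow-up data are lost, since outcomes not collected cannot be restored at the analysis stage.

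**What to change.** Replace the exclusion sentence under Interventions with:

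> Use of other treatment is recorded as a protocol deviation with date and type; the participant stays in follow-up and is analysed in the allocated group.

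State the period over which the restriction applies. Make the as-randomised analysis primary, and report the analysis without these participants as a sensitivity analysis. The restriction on co-treatment is a clinical matter and is left unchanged.

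The cost is an edit to the protocol, a deviation field on the record form, and continued measurement of a few participants at visits already scheduled. The small downside is some possible dilution of the as-randomised effect if other treatment helps those who take it; the sensitivity analysis, set beside the recorded deviations, shows how far the result depends on these participants.

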#### Group 1: manual therapy

The “manual therapy” protocol will consist of three techniques based on scientific evidence for the treatment of neck pain [31–33]. These techniques represent a very close approximation to the treatment that is performed in the daily clinic, outside the research protocols.

This protocol will be applied in the three treatment sessions, one per week.High thoracic manipulation on T4 [31]Cervical articular mobilization (2 Hz, 2 min × 3 series) [32]Suboccipital muscle inhibition (3 min) [34].

#### Group 2: therapeutic exercise

The “therapeutic exercise” protocol will be taught to patients in the first session and should be done once a day during the 3 weeks of treatment. It will be reinforced by the physiotherapist in each of the three individual sessions.

##### Week 1. Exercises 1 and 2:

Cranio-cervical flexion (CCF) in supine position with towel in the posterior area of the neck (3 sets, 10 repetitions, 10 s of contraction each repetition with 10 s of rest)CCF sitting (3 sets, 10 repetitions, 10 s of contraction each repetition with 10 s of rest)

##### Week 2. Exercises 1, 2, 3, and 4:

3.Co-contraction of deep and superficial neck flexors in supine decubitus (10 repetitions, 10 s of contraction with 10 s of rest)4.Co-contraction flexors, rotators, and inclines. Patient will perfom cranial nerve flexion, while physiotherapist asks him to tilt, rotate, and look toward the same side while he opposes a resistance with his hand (10 repetitions, 10 s of contraction with 10 s of rest)

##### Week 3. Exercises 1, 2, 3, 4, 5, and 6:

5.Eccentric for extensors. With the patient seated, should perform cervical extension, then they must realize a CCF and then finish doing a cervical flexion (10 repetitions)6.Eccentric for flexors. The patient will be in quadrupedal and neutral neck position. He should perform neck flexion, and then must realize a CCF and, maintaining that posture, extend the neck and then finally lose the CCF (10 repetitions).

#### Group 3: sham treatment

For the “control” protocol, the patient will be placed in the supine position, while the physiotherapist will lay his hands without therapeutic intention on the patient’s neck for 3 min, the physiotherapist will simulate the technique of suboccipital inhibition [34]. Later, with the laser pointer off, the patient will be contacted without exerting pressure for 10 s. Patients assigned to the control group will receive treatment 1 or 2 after completing the study.

### Outcome measures

#### Neck Disability Index (NDI)

The NDI is a self-assessment instrument of the specific functional status of subjects with neck pain with 10 elements, including pain, personal care, weight gain, reading, headache, concentration, work, driving, sleeping, and leisure. Each section is rated on a scale of 0 to 5, where 0 means “painless” and 5 means “the worst pain imaginable.” The points obtained are added to a total score. The questionnaire is interpreted as a percentage. The disability categories for NDI are 0–8%, without disability; 10–28%, mild; 30–48%, moderate; 50–64%, serious; and 70–100%, complete [35, 36].

#### Visual analog scale (VAS) for pain

The subjects participating in the study will indicate the intensity of their pain by means of a VAS of 100 mm. They must signal on a horizontal line of 100 mm where they would place their pain, where 0 mm indicated “no pain” and 100 mm would be “the worst pain imaginable” [37].

#### Pressure Pain Threshold (PPT)

The PPT is recorded in newtons/square centimeter using a digital algometer (Force Ten™ -Model FDX; Wagner, Greenwich, CT, USA) with a round tip surface area of 1 cm^2^. The measurement is taken on the spinous process of vertebra C2, the evaluator gradually increasing the pressure until the patient indicates through a “Yes” when the pain or discomfort appears. Three measurements are taken, obtaining an average value of these three measurements for the statistical analysis [38, 39].

#### Overall Balance Index (OBI)

We obtain the OBI measurement through a dynamic stabilometric platform (Balance System™ SD; Biodex, Shirley, NY, USA). The General Stability Test is applied at level of difficulty 4, with 1 being the most and 8 the least difficult level. The platform is free in the anterior-posterior and medial-lateral axes, and it allows one to obtain the OBI through deviations with respect to a zero point established before the test, with the platform stable. Two 20-s tests are performed, with 1 min between each test, with the score of the second test chosen for the statistical analysis. The index is calculated through the anterior-posterior and medial-lateral relationship + standard deviation [40, 41].

These variables will be measured in the pre-evaluation, first evaluation (week 2), second evaluation (week 4, short-term), and third evaluation (week 12, medium term). These evaluations will be carried out by an evaluator trained in these procedures, and the data will be stored in an Excel document.

### Participants’ timeline

A brief Standard Protocol Items: Recommendations for Interventional Trials (SPIRIT) schedule is provided in Fig. 1, and a populated SPIRIT checklist is provided in Additional file 1.

**Fig. 1 Fig1:**
[figure not shown]
SPIRIT schedule for patient participation

### Sample size calculation

The sample size was calculated using the Granmo calculator v.7.12. Based on the analysis of the variance of means, and estimating an alpha risk of 5% (0.05), a beta risk of 10% (0.10), a unilateral contrast, a typical deviation of 10% (0.10), a minimum difference to detect of 9.8% (0.098) which is based as the minimum clinically important differences in OBI [42], and a rate of follow-up losses of 15%, 10 subjects are required in each group, assuming that there are three groups. Finally, we will include 66 patients who will be divided into three groups, each group with at least 20 subjects, so as to overcome this value to assume the possible loss of follow-up.

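### The stated requirement of 10 subjects per group does not follow from its own inputs; any between-group comparison with a largest difference of 0.098 needs at least 18 evaluable per group

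*Protocol article*

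**What the plan says.** The Sample size calculation section of the Protocol article bases the number on an analysis of variance of means with three groups. Its inputs are a 5% alpha, a 10% beta, "a unilateral contrast", "a typical deviation of 10% (0.10"), "a minimum difference to detect of 9.8% (0.098") and "a rate of follow-up losses of 15"%. The difference is described as the minimum clinically important one for the Overall Balance Index. The section concludes that "10 subjects are required in each group, assuming that there are three groups".

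It then sets enrolment at 66 in three groups, "each group with at least 20 subjects, so as to overcome this value to assume the possible loss of follow-up". The Randomization section specifies balanced allocation, so 66 means 22 per group. The Statistical analysis section plans a one-factor ANOVA between groups with Bonferroni post hoc contrasts, and repeats the 90% power.

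**The concern.** A standardised difference of 0.098/0.10 = 0.98 is large, but 90% power to separate two independent groups at that difference takes clearly more than 10 per group, all the more so once losses are included.

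The figure matters because the article uses it as the yardstick for 66: the planned number is explained as exceeding 10 so that losses can be absorbed. If the true requirement is close to or above 22 per group, that explanation fails, and a reader cannot tell from the article how much loss the trial can bear or what power its planned analysis has.

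**Working it through.** **Inputs**, all from the Sample size calculation section: alpha 0.05 one-sided (z = 1.645); power 0.90 (z = 1.282); SD 0.10; difference 0.098, so d = 0.98; losses 15%, so enrolled = evaluable/0.85; three groups, taken as equal in size (Randomization section).

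**Step 1. Can 10 be reproduced?** A figure near 10 came out of only two set-ups.

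- One-sample or paired formula: (1.645 + 1.282)²/0.98² = 8.92; 8.92/0.85 = 10.5. This omits the factor 2 needed to compare two independent groups.
- Three-group ANOVA with means 0, 0.098 and 0.196: 8 evaluable per group; 8/0.85 = 9.4, so 10. Here the extreme groups differ by 0.196, twice the stated difference.

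The article states neither.

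**Step 2. Most lenient between-group reading: one pairwise comparison, one-sided, no multiplicity adjustment.**

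- Normal approximation: n = 2(1.645 + 1.282)²/0.98² = 17.8, so 18 evaluable. Enrolled: 17.8/0.85 = 20.98, so 21 (or 18/0.85 = 21.2, so 22, if rounded first).
- Exact t test: 19 evaluable; 19/0.85 = 22.4, so 23 enrolled.

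**Step 3. Three-group ANOVA, F test at alpha 0.05, 90% power, largest difference 0.098 (noncentral F).**

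| Means | Evaluable per group | Enrolled per group |
|---|---|---|
| 0, 0.098, 0.098 | 21 | 24.7, so 25 |
| 0, 0.049, 0.098 | 28 | 32.9, so 33 |

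Running the F test at alpha 0.10, as a loose counterpart of a one-sided test, gives 18 and 23 evaluable for the same two patterns. That is still nowhere near 10.

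**Step 4. What the planned enrolment delivers.** 22 × 0.85 = 18.7 evaluable per group. If the minimum of 20 means enrolled, 20 × 0.85 = 17 evaluable.

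| Test at difference 0.098, SD 0.10 | Power at 18.7 per group | Power at 17 per group |
|---|---|---|
| One pairwise t test, one-sided, unadjusted | about 90% | about 88% |
| ANOVA F test, alpha 0.05, means 0, 0.098, 0.098 | 86% | 82% |
| ANOVA F test, alpha 0.05, means 0, 0.049, 0.098 | 74% | 70% |
| Two-sided Bonferroni contrast, three comparisons (two-group t test at 0.05/3) | about 68% | about 63% |

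**Step 5. What 10 per group would deliver.** 10 × 0.85 = 8.5 evaluable, which gives about 61% for the one-sided pairwise t test and 38% to 48% for the two ANOVA patterns, against the stated 90%. The article does not plan a trial of that size; the figures only show how far 10 is from meeting the stated inputs.

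**The case against.** The strongest defence is that the article names ANOVA with three groups and gives no pattern of means. If 0.098 is the smallest gap between neighbouring groups, the means are 0, 0.098 and 0.196, and 8 evaluable inflated by 15% losses does give 10. It is true that the document does not settle which route was used. But the section does not state that pattern, and an F test does not fit a one-sided contrast. The Hypothesis section also says only that the experimental treatments do better than sham, not that one of them beats the other by a further 0.098. The defence explains how 10 might have arisen; it does not make 10 the requirement for the stated difference.

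The second defence is that 66 will be enrolled whatever the calculation says, and this limits the point. A reader might infer that the trial is underpowered on its own stated terms. The document does not support that: on a single unadjusted one-sided comparison, 22 per group keeps about 90% power after 15% loss. A reader might also say that the article claims a two-fold margin. It does not; it says only that the group size exceeds the calculated value to allow for losses, and the ratio of 20 to 22 against 10 is the reader's own arithmetic.

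Third, the minimum of 20 per group is not labelled as enrolled or remaining. If it means remaining, pairwise one-sided power is about 92% and the floor causes no shortfall on that test.

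**Conclusion.** The figure 10 is wrong for the comparison described. The requirement is understated by a factor of about 1.8 to 2.8 in evaluable subjects (18 and 28 against 10), and by 2.1 to 3.3 when enrolled numbers are compared (21 and 33 against 10, since the 15% loss is listed among the inputs to the 10).

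The result rests on the article's own inputs and on two assumptions: equal groups, and 0.098 as the largest difference between groups. Only a pattern with extreme groups further apart, which the article does not state, brings the number down to 10.

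Enrolment of 66 meets the most lenient reading almost exactly, with no meaningful reserve. It does not reach 90% for the ANOVA and Bonferroni contrasts in the Statistical analysis section. It would be equally wrong to replace 10 with a statement that 22 per group satisfies the requirement: that rests on one unadjusted comparison, and the exact t calculation with losses already rounds up to 23.

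**What to change.** Keep enrolment at 66 and rewrite the Sample size calculation paragraph:

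1. Delete the figure of 10 per group and the statement that the planned group size exceeds it.
2. State which test the calculation is for and, if it is the ANOVA, the pattern of means assumed.
3. Report what 22 enrolled per group (18.7 evaluable after 15% loss) delivers at a difference of 0.098 and SD 0.10: about 90% for one unadjusted one-sided pairwise t test, about 74% to 86% for the ANOVA F test at alpha 0.05, and about 68% for a two-sided Bonferroni contrast over three comparisons.
4. Say that there is essentially no spare margin for losses above 15%.
5. Say whether the minimum of 20 per group means enrolled or remaining. If enrolled, add that the 17 evaluable give about 88% even on the most lenient test.

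The cost is one reworded paragraph and no extra patients. The only downside is a less favourable stated figure.
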